### Data Analysis

For aim 1, we will transcribe and analyze qualitative data from participants using NVivo 10 qualitative data analysis software (QSR International) [26]. Each interview will be transcribed and coded after the collection. We will use a thematic content analysis informed by framework [27] and inductive–deductive hybrid [28] methods. Themes will be extracted to inform the adaptations of NF-Web.

For aim 2, we will test feasibility according to the proportion of participants who agree to participate from those who express interest. Acceptability will be calculated as the number of participants who complete the web program and provide a posttest from those who start the program. We will assess the credibility of the web program using the Credibility Questionnaire (means, SDs, and IQRs) [25]. We will measure satisfaction with the web program using the Client Satisfaction Questionnaire (means, SDs, and IQRs) [24]. We will measure user experience with the User Experience Questionnaire (means, SDs, and IQRs) [23] and qualitative exit interview data. Upon completion, we will explore within-group improvements in NF-Web from baseline to posttest. Our hypotheses are that there will be positive within-group improvements in the secondary outcomes of NF-Web.

For our quantitative analyses, we plan to use linear contrasts to compare changes in secondary (QoL, emotional distress, pain) variables from baseline to posttest within the NF-Web intervention. For QoL outcomes that have established minimal clinically important differences [29], we will consider improvements from baseline to posttest to be clinically meaningful if the mean improvement is above 6.25.

We expect to use SPSS 25 software (IBM Corporation) for the statistical analyses, with an analytic strategy that mirrors the efficacy trial [11]. As our study is a small open pilot trial, we will not be adequately powered to detect within-group or between-groups differences for quantitative outcomes. We will also not be able to examine demographic variables beyond their descriptive aspects. Even so, baseline to posttest will be explored for each outcome in NF-Web, with descriptive statistics and signals of improvement being reported as relevant. If the NF-Web program confirms the primary outcomes (feasibility or acceptability) and trends positively for the secondary outcomes, we will consider this to be preliminary evidence that NF-Web is a useful psychosocial web-based program.

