Although virtual delivery increased the reach of our intervention and allowed the recruitment of geographically diverse individuals, ongoing barriers impede all people with NF from enrolling. Our ongoing DoD-funded RCT receives interest from patients across the globe; yet, time-zone differences (eg, a difference of 10.5 hours between EST and Indian Standard Time); occupational or family obligations; limited and convenient scheduling (eg, 10 PM local time, weekend scheduling); 8-week, 90-minute weekly scheduling; and severe actual or perceived appearance concerns (eg, cutaneous and plexiform neurofibromas with facial tumors, palsy, café au lait spots, freckling) cause people to decline participation (approximately 30% who are contacted) [7]. As there is a lack of trained providers to administer evidence-based psychosocial care, a web-based platform (ie, a program hosted on a website server and created using HTML) in addition to the live videoconferencing program allows for asynchronous delivery of the intervention and could bypass these barriers to participation.

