### Setting

Studies related to both aims 1 and 2 will be conducted at a large northeastern academic medical center in the United States. Our use of virtual recruitment and web-based intervention delivery allows participants from the United States as well as the rest of the world to engage in the study at their convenience (eg, location, time of day, pace). We will recruit participants through our research tracking log that contains both efficacy trial completers (assessments complete at 1 year time point; aim 1) and participants who expressed interest in the 3RP-NF live video program but could not participate because of treatment barriers (aim 2).

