### Recruitment

For aim 1, we will first email participants who were randomized to the 3RP-NF intervention and completed the last assessment point of our efficacy trial and invite them to participate in a live video qualitative interview with a trained clinical psychologist with expertise in NF (50 min). We will use purposive sampling to achieve population-consistent representation of the three NF types (NF1, n=10; NF2, n=6; and schwannomatosis, n=4). We will recruit more participants if we do not achieve theme saturation. If participants meet enrollment criteria and are interested in participating, they will receive the consent form to review and return through secure email. After obtaining consent, we will schedule the participants for an interview.

For aim 2, we will recruit participants (n=30; approximately 15 per cohort) for the open pilot phase of NF-Web. These will be participants who previously expressed interest in participating in the live video program but ended up not participating because of treatment barriers. The study staff will describe the trial, and all participants will be screened by the study staff over the phone. The screening procedures are the same as those outlined in the 3RP-NF efficacy trial protocol [11].

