### Screening and Enrollment

The clinical research coordinator (CRC) will obtain informed consent and ask the participants to return the signed consent form electronically through secure email. Participants are considered enrolled in the study when signed consent is received. The CRC will schedule a time with each enrolled participant for their individual semistructured video interview. We will provide an additional overview of the study procedures at the beginning of each interview. The study interviewer will ensure that the participants understand the study procedures and that we will audio record the interview. The participants will be interviewed on (1) experiences of living with NF; (2) experience during the live video program (ie, efficacy trial); (3) attitudes and perceptions of NF-Web, including participation barriers and facilitators; (4) perceptions about modifying session content and skills; and (5) considerations for decreasing barriers to participation. We will save audio on a secure and password-protected computer.

For aim 2, we will recruit participants who could not participate in the efficacy trial using the tracking log for our efficacy RCT. We will email or call the potential participants. We will screen participants over the phone to ensure that the eligibility criteria are met. The research staff will cover important components of the study protocol, and we will ask eligible participants to return the informed consent document to the CRC electronically through secure email.

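### Acceptability is calculated over participants who start NF-Web, so anyone who consents but never starts counts towards feasibility and drops out of acceptability; the feasibility denominator can be read two ways

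*Protocol article*

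**What the plan says.** The Data Analysis section of the protocol article states both rates.

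- Feasibility: "we will test feasibility according to the proportion of participants who agree to participate from those who express interest".
- Acceptability: "Acceptability will be calculated as the number of participants who complete the web program and provide a posttest from those who start the program".

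It does not say what counts as expressing interest, agreeing or starting.

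On who is approached for aim 2, the Recruitment section says: "These will be participants who previously expressed interest in participating in the live video program but ended up not participating because of treatment barriers". The Setting section describes the tracking log in the same way: "participants who expressed interest in the 3RP-NF live video program but could not participate because of treatment barriers (aim 2". Under Screening and Enrollment, staff work from that log ("We will email or call the potential participants"), then screen by phone and obtain consent.

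On the order of events after consent, NF-Web Platform and Procedures places the baseline assessments first, then an account-setup email, then log-in. The Assessments section provides for staff to chase and help consented participants who have not completed baseline after a week. Screening and Enrollment fixes enrolment at consent ("Participants are considered enrolled in the study when signed consent is received"). That sentence stands in the aim 1 paragraph, but the aim 2 procedures follow the same order.

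The Results section reports that the target of 30 was reached and that 24 completed the program and the posttest. It does not report how many were contacted, expressed interest or started.

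**The concern.** The two rates should together follow people from approach to completion. As defined, they leave a gap between consent and first use. Agreeing puts a person in the feasibility numerator; only starting puts a person in the acceptability denominator. Someone who consents and never opens the program counts in favour of feasibility and is never counted against acceptability. For a self-paced program with no live clinician, failing to begin is one of the main ways in which it can prove unacceptable.

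The feasibility denominator raises a second question. If expressing interest means responding with interest in NF-Web, people who are emailed or called and refuse or do not reply fall outside the rate. If it means the interest they showed earlier in the live program, they stay in.

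This matters because these rates carry the study's conclusion. The Objective section sets them against prespecified benchmarks, and the Data Analysis section makes confirming feasibility or acceptability a condition for calling NF-Web a useful program.

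**Working it through.** The document states no feasibility rate, acceptability rate or numeric benchmark, so there is no figure of its own to reproduce. The planned size is consistent: 2 cohorts × about 15 = 30.

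**Acceptability**

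Inputs: 30 recruited and 24 completing program and posttest (Results). I take recruited to mean consented. Non-completers: 30 − 24 = 6. Let k be the number of these 6 who consented but never started; k is not reported, so the whole range is shown.

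- Over all consented: 24/30 = 80.0%. The exact (Clopper–Pearson) 95% limits are the 2.5% quantile of Beta(24, 7) and the 97.5% quantile of Beta(25, 6), giving 61.4% to 92.3%.
- As defined in the plan: 24/(30 − k).

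| k (assumed) | Ratio | Rate | Exact 95% CI |
|---|---|---|---|
| 0 | 24/30 | 80.0% | 61.4% to 92.3% |
| 1 | 24/29 | 82.8% | 64.2% to 94.2% |
| 2 | 24/28 | 85.7% | 67.3% to 96.0% |
| 3 | 24/27 | 88.9% | 70.8% to 97.6% |
| 4 | 24/26 | 92.3% | 74.9% to 99.1% |
| 5 | 24/25 | 96.0% | 79.6% to 99.9% |
| 6 | 24/24 | 100% | 85.8% to 100% |

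Since 30 − k ≤ 30, the planned rate is never below the all-consented rate. The difference is 0 to 20 percentage points.

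**Feasibility**

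*Reading A: earlier interest in the live program.* By the Setting and Recruitment sections, everyone in the aim 2 pool has already expressed that interest. All who are contacted are then in the denominator, and the loss is 0 points.

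*Reading B: new interest in NF-Web.* Let I be the number interested and s the share of those contacted who never express interest. Contacted = I/(1 − s), so agree/contacted = (agree/I) × (1 − s). With 30 agreeing, and with I and s assumed:

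| I (assumed) | Stated, 30/I | s = 10% | s = 30% | s = 50% |
|---|---|---|---|---|
| 35 | 85.7% | 77.1% | 60.0% | 42.9% |
| 40 | 75.0% | 67.5% | 52.5% | 37.5% |

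For example, with I = 40 and s = 30%: contacted = 40/0.7 = 57.1, and 30/57.1 = 52.5%. These figures show only how far the two readings can diverge. They do not estimate what happened in the trial.

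**The case against.** **Feasibility.** The plan describes the whole aim 2 pool as people who had already expressed interest, in almost the same words as the feasibility denominator, and the recruitment steps run from contact to screening to consent with no separate expression of interest. On that reading every refusal is counted. This stands. A reader might infer that both rates are inflated by construction; for feasibility the documents do not support that. What remains is an ambiguity: the Data Analysis wording does not say which interest is meant, and the two meanings give different rates.

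A reader might also think that the feasibility rate cannot be compared with the Background figure on the live-video trial, where barriers "cause people to decline participation (approximately 30% who are contacted"). That figure is motivation only, and no comparison with it is planned.

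**Acceptability.** Completion among those who start is a legitimate measure of how the program is received by people who use it. No non-starter is reported, and staff help with baseline questionnaires and account setup, which narrows the gap. *Start* might be operationalised at account setup. The counts of 30 and 24 are published, so a reader can work out 80% unaided. Each of these is fair. None changes the definition: the plan's rate excludes consented non-starters, and an undefined start leaves the denominator open to choice after the data are known. It is also true that an article may leave operational detail to a fuller document. But this article states the two ratios itself, and the mismatch lies in what it states.

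**Conclusion.** The point holds for acceptability. The stated denominator leaves out people who consent and never start, while feasibility counts them as successes, so acceptability can only equal or exceed the all-consented rate. On the reported counts that is 80.0% against anything from 80% to 100%. This rests on recruited meaning consented and on the unreported number of non-starters among the 6 non-completers; if all 30 started, the difference is nil.

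For feasibility the finding is limited to an ambiguous denominator: no loss under one reading, and a loss of unknown size under the other.

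A reader might go on to infer that the choice of denominator would carry the study past its benchmark. That cannot be said, because the article refers to benchmarks set in advance but gives no number.

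**What to change.** - **Acceptability:** make all consented aim 2 participants the denominator. Keep the rate among starters as a supplementary figure, and define what counts as starting (for example, first log-in).
- **Feasibility:** state that the denominator is everyone contacted from the tracking log and not found ineligible, with refusals and non-responders counted and listed separately. This gives the same rate under either reading of interest.
- **Reporting:** give the numbers contacted, ineligible, refused, not responding, consented, started and completed, with exact 95% confidence intervals for both rates.

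The cost is a few sentences in the analysis plan. The tracking log and the study's consent and log-in records should already hold the counts. The one drawback for the sponsor is that the headline rates may be lower.

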### Objective

The purpose of this study is to develop the first web-based platform of a mind–body program for adults with NF with stress and difficulties in managing NF symptoms. Our first aim (aim 1) is to adapt the adult mind–body program, 3RP-NF, for web-based delivery using qualitative data from semistructured interviews with participants who completed the efficacy trial. To achieve this aim, we will collect information about the participants’ experiences, perceptions of a web-based platform, and willingness to participate. We will use this information to develop a web-based platform—Neurofibromatosis Web (NF-Web)—that will be designed to be compatible with desktops, laptops, and mobile devices (eg, smartphones and tablets). We expect that participants from the efficacy trial will be willing to participate in semistructured interviews and provide meaningful feedback to inform the adaptation of the 3RP-NF intervention for web-based delivery. Our second aim (aim 2) is to optimize NF-Web through at least two subsequent open pilot studies with exit interviews. For each open pilot, we aim to optimize the feasibility and acceptability of NF-Web and explore the quantitative outcomes. We hypothesize that the final iteration of NF-Web will meet the a priori set feasibility and acceptability benchmarks [8-10]. We also hypothesize that participation in NF-Web will be associated with improvement in quantitative outcomes from baseline to posttest.

Related to the aims and scope of this pilot study, we will not be testing the use of different technologies for NF-Web delivery (eg, mobile and tablet vs desktop or laptop modalities); nor are we directly interested in the acceptability of such technologies (eg, the advantages of the website over the live video program). Rather, we are interested in studying the psychosocial program itself as a web-based tool to deliver the mind–body program to participants who typically have a higher burden when accessing psychosocial care. The creation of NF-Web essentially involves taking an efficacious program, which is delivered either in person or through live video by a trained clinical psychologist, and making it more accessible by delivering it through a web-based platform. Here, we describe our methodology for both the study aims.

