## Methods

### Study Design

For aim 1, we will conduct individual qualitative semistructured interviews to adapt the 3RP-NF intervention for web-based delivery. For aim 2, we will conduct at least two subsequent open pilot studies of NF-Web to optimize feasibility and acceptability and explore changes in the quantitative outcomes (Figures 1 and 2). We will modify NF-Web after each open pilot to maximize feasibility and acceptability, as needed.

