#### NF-Web Platform and Procedures

NF-Web is a website version of the 3RP-NF program [11]. We anticipate that NF-Web will have 8 sessions (Textbox 2) with content presented in multiple modalities (eg, written, audio, video, interactive components) and administered entirely on the web without a live clinician.

After participants provide consent and complete baseline assessments, we will send them an email with detailed information on how to begin the web-based intervention (ie, *NF-Web Account Setup* email). NF-Web will require a secure log-in to access content with a username assigned by the study staff (eg, MGHNFW01) and a unique password. The CRC will keep a log of all usernames and passwords on a password-protected computer. We will give participants website instructions through email and review the terms and conditions of use provided on the website, which will include limits to confidentiality (risks similar to usual internet use; disclosure at their discretion) and ways to protect their information. The study staff will be available to answer all participant questions and concerns during the initial account creation and setup for the program.

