After enrollment, participants will log in to NF-Web and progress through the web-based program at their own pace for 8 weeks (streaming video content embedded from YouTube; no software download required). Each week, participants will view session content consisting of mind–body video modules, audio recordings, written text, quizzes, and homework assignments (submitted through email or the web platform) from the 3RP-NF program. The participants will have access to completed session content from previous weeks as they await the following week’s session after completing the weekly assignments (viewing videos, completing in-session exercises and quizzes). In addition, participants will be informed of the optional discussion board where they can directly post content (deidentified for the trial owing to institutional review board requirements; data used to potentially assess user experience and engagement ethnographically). The participants will also have the option (ie, opt in or out) at the beginning of the program to receive daily or weekly sessions and skill practice reminders through email and text messages. Sessions will be unlocked by the study staff and administered weekly to the participants to pace their learning and practice (ie, new content available each week). We will have 2 cohorts of participants for each round (2 rounds of approximately 15 each, n=30) to attempt simulation of the NF-Web platform components (eg, discussion board use and monitoring, administrative tasks). The treatment fidelity for NF-Web mirrors that of the efficacy trial [11], with the addition that all materials for NF-Web will be prerecorded. At any point during the study, the participants will be able to ask nonurgent questions by sending an email to the study staff through a secure website form on NF-Web. This approach to the website may be modified or adapted before being finalized based on participant feedback gathered in the aim 1 exercise.

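### Feasibility is measured as agreement to take part, which is settled before anyone uses NF-Web, yet it is treated as something that revising the site will improve

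*Protocol article*

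**What the plan says.** The Methods part of the abstract lists feasibility among the primary outcomes. The Data Analysis section defines it: "we will test feasibility according to the proportion of participants who agree to participate from those who express interest". Acceptability is defined next to it as completing the program and giving a posttest, among those who start.

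Three places treat feasibility as a property of the site version:
- The Objective part of the abstract sets out to optimise the platform's feasibility iteratively.
- Study Design: "We will modify NF-Web after each open pilot to maximize feasibility and acceptability, as needed".
- The Objective section of the Introduction: "For each open pilot, we aim to optimize the feasibility and acceptability of NF-Web and explore the quantitative outcomes", followed by "We hypothesize that the final iteration of NF-Web will meet the a priori set feasibility and acceptability benchmarks".

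The last paragraph of Data Analysis says what the result is for. If the primary outcomes, glossed there as feasibility or acceptability, are confirmed and the secondary outcomes trend positively, this counts as preliminary evidence that NF-Web is useful.

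**The concern.** The measure and its stated use do not fit. Agreement to take part describes how candidates respond to an invitation. Revising the site changes what they meet after they have accepted. A proportion completed at the first step does not directly respond to a change made at the second.

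Two things are at stake. First, Data Analysis can be read as allowing feasibility alone to carry the primary part of the conclusion, so a good uptake figure could be reported as evidence about a platform that those people had not yet used. Second, there is a gap between the two proportions. A person who consents and then never gets into the program is a success for feasibility and is missing from acceptability. For a stand-alone site delivered without a live clinician, failure to start is one of the main things a pilot should detect.

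**Working it through.** **Step 1: when each person's feasibility result is fixed.** Under Recruitment and Screening and Enrollment, aim 2 candidates are contacted from the efficacy-trial log, told about the trial by staff and screened by telephone. Viewing the site before consent is not mentioned. NF-Web Platform and Procedures then gives the order:
- "After participants provide consent and complete baseline assessments, we will send them an email with detailed information on how to begin the web-based intervention"
- "NF-Web will require a secure log-in to access content with a username assigned by the study staff"
- "After enrollment, participants will log in to NF-Web and progress through the web-based program at their own pace for 8 weeks"

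Screening and Enrollment adds "Participants are considered enrolled in the study when signed consent is received". That sentence stands in the aim 1 paragraph, but the three statements above establish the same order for aim 2 without it. Whether agreement means a verbal yes or a signed form, it comes before first log-in.

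**Step 2: how each kind of candidate is counted.**

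| Candidate | Feasibility | Acceptability |
|---|---|---|
| Interested, declines | failure | not counted |
| Consents, never starts | success | not counted |
| Starts, does not finish or gives no posttest | success | failure |
| Completes program and posttest | success | success |

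The second row is the gap: neither proportion registers the failure to start.

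**Step 3: how large the gap could be here.** The planned size reproduces: 2 cohorts × 15 = 30. Results says the target of 30 was met and that 24 completed the program and posttest. Assume that exactly 30 consented, and let k be the number who consented but never started. The article does not give k. It can be at most 30 − 24 = 6.

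Acceptability as defined = 24 / (30 − k):
- k = 0: 24/30 = 80.0%
- k = 3: 24/27 = 88.9%
- k = 6: 24/24 = 100%

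Feasibility = 30 / (number who expressed interest). The denominator is not stated, but k does not enter the formula, so feasibility is the same in all three cases.

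Completion among all who consented = 24/30 = 80% whatever k is (exact 95% interval 61% to 92%).

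The more people fail to start, the better acceptability looks, and feasibility does not move. The proportion among all who consented is unaffected by this. The article gives no counts by cohort, so nothing can be computed for the two site versions separately.

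**The case against.** Four points on the other side deserve weight.

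1. **Agreement is a recognised feasibility measure and suits this study's rationale.** NF-Web exists because barriers kept people out of the live program. The share of those people who accept a web format says something about whether the format is feasible for them. This stands, and it is a reason to keep the proportion under a more exact name.

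2. **A site revision could reach candidates indirectly.** A reader might infer that modifying NF-Web cannot change feasibility at all. The documents do not support that. Staff describe the trial before consent, and a change in length, pacing or reminders could enter that description. No such route is planned, however, and any effect would come through the description and not through use of the site.

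3. **No comparison of feasibility between cohorts is planned.** A reader might infer that a rise from the first cohort to the second will be credited to the revision. Nothing in the article says so. The hypothesis is that the final version meets benchmarks, and the abstract says refinement follows participant feedback. Chance variation between cohorts is therefore no part of this point.

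4. **Much evidence is collected after exposure.** Acceptability, satisfaction, credibility, the weekly user-experience questionnaire and the exit interviews all follow use of the site. It would be wrong to infer that the optimisation plan as a whole cannot be evaluated.

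The sources for the benchmarks and the full protocol are not shown, and further feasibility measures may exist there. That does not remove the mismatch, because the article itself fixes both the definition and the use made of it.

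**Conclusion.** The point holds in a limited form. Feasibility as defined is complete before anyone uses NF-Web. It is therefore not a direct measure of what revising the site achieves, and alone it should not support a conclusion about the platform. Acceptability does not fill the gap, because people who consent but never start are outside its denominator.

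With the reported 24 completers and an assumed 30 who consented, that gap leaves acceptability anywhere between 80% and 100%. This range rests on 30 being the number who consented and on k being unknown. It does not show that anyone failed to start.

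The wording about feasibility or acceptability may be a loose gloss and not a deliberate either-or rule, but as written it permits the weaker reading. The point is worth correcting before results are reported. It does not undermine the other outcomes or their use in refining the program.

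**What to change.** - In Data Analysis, keep the present proportion and label it recruitment feasibility. In Study Design and Objective, do not present it as something that site revisions will raise.
- Report by cohort, with everyone who consented as the denominator, (a) the proportion who set up the account and finish session 1, and (b) the proportion who complete the program and the posttest.
- Base the closing statement on whether NF-Web is useful on these measures taken after access, not on the consent proportion alone.

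The cost is a few sentences and some tabulation. Account setup, weekly unlocking of sessions by staff and REDCap surveys are existing procedures, so no new participants or instruments are needed. The team should confirm that the account and unlocking records were kept in usable form.

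There are two drawbacks. The figures may look less favourable than a consent rate among interested people. Also, Results says the pilot had ended with analysis still to come, so the measures should be marked as added after the pilot ended and should not be presented as prespecified primary outcomes.
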